# Early implantation of a transjugular intrahepatic portosystemic shunt (TIPS) in patients with liver cirrhosis and ascites (eTIPS): a multicentre, randomised controlled trial

**DOI:** 10.1186/s13063-025-09038-8

**Published:** 2025-10-02

**Keywords:** Cirrhosis, Ascites, Transjugular intrahepatic portosystemic shunt, Transplantation, Survival

## Abstract

**Background:**

Portal hypertension is a major complication in patients with liver cirrhosis, leading to severe outcomes such as variceal bleeding and ascites. Transjugular intrahepatic portosystemic shunt (TIPS) has emerged as an effective interventional treatment of recurrent ascites and variceal bleeding. However, up to 30% of patients with recurrent ascites show TIPS refractory ascites, and prior data have shown that the frequency of paracenteses before TIPS implantation predicts ascites clearance indicating that TIPS implantation may be too late in some patients. Especially, patients with grade 2 ascites and a MELD score ≥ 15, or grade 3 ascites irrespective of MELD score at first decompensation with ascites face a high risk of further decompensation and mortality. Therefore, these patients may benefit from early TIPS implantation in order to improve post-TIPS mortality. We hypothesise that early TIPS implantation in these selected patients at the time of the first decompensation may improve transplantation-free survival compared to standard medical treatment (SMT).

**Methods:**

The eTIPS study is a prospective, randomised, open, multicenter interventional, superiority trial. Patients will be randomised 1:1 in the intervention group with TIPS implantation and in the SMT group. The primary endpoint is transplantation-free survival. Secondary endpoints include the time to ascites with need for paracentesis and quality of life assessed six and 12 months after randomisation.

**Discussion:**

Expanding the concept of early TIPS implantation to ascites management may offer significant survival benefits and may significantly change the treatment algorithm of patients with ascites.

**Trial registration:**

German Registry for Clinical Studies DRKS00034545. Registered on 20/02/2025.

Clinical trials NCT06576934. Registered on 04/12/2024.

## Administrative information

Note: the numbers in curly brackets in this protocol refer to SPIRIT checklist item numbers. The order of the items has been modified to group similar items (see http://www.equator-network.org/reporting-guidelines/spirit-2013-statement-defining-standard-protocol-items-for-clinical-trials/).

## Introduction

### Background and rationale {6a}

Portal hypertension is a hallmark of liver cirrhosis leading to oesophageal and gastric varices, variceal bleeding and ascites [1–3]. These complications may trigger further complications such as hepatorenal syndrome and spontaneous bacterial peritonitis, and they are associated with significant morbidity and mortality [2, 4]. Implantation of a transjugular intrahepatic portosystemic shunt (TIPS) is a safe and effective interventional treatment for portal hypertension, and TIPS implantation has emerged as a major component within the treatment algorithm for portal hypertension [5, 6]. The most common indications for TIPS implantation are secondary prophylaxis of variceal bleeding and recurrent or treatment refractory ascites [5]. According to recent evidence, early TIPS (i.e. pre-emptive TIPS) within the first 72 h following the bleeding event in patients with acute variceal bleeding and a high risk of re-bleeding (CHILD–Pugh C < 14 or CHILD–Pugh B > 7 with active bleeding in index endoscopy) is associated with improved survival [7]. Even patients with acute-on-chronic liver failure (ACLF) after variceal bleeding show a survival benefit after pre-emptive TIPS implantation [8]. Therefore, the concept of early TIPS implantation after variceal bleeding is recommended by current guidelines [1, 7].

In contrast, patients with ascites are allocated to TIPS implantation at later stages of disease (treatment refractory or recurrent ascites) when diuretic treatment and large-volume paracenteses (LVP) do not lead to sufficient ascites control [1]. The clinical benefit of TIPS implantation has been confirmed in several randomised controlled trials, although these studies showed very heterogeneous results with respect to improvement of survival [1, 9–11]. In the majority of these studies, uncovered stents were used, but today, the use of covered stents is exclusively recommended due to their superior patency. Only in the study by Bureau et al. covered stents were used, and thus this study may be considered representative for everyday clinical practice [12]. A clear survival benefit for patients allocated to TIPS implantation was shown, and the prevalence of post-TIPS hepatic encephalopathy (HE) was not increased in these patients. Patients who received TIPS implantation due to recurrent or refractory ascites show ascites clearance without the need for further paracenteses in only 51% to 68% [1, 11]. In contrast, the study by Bureau et al. reported a significantly improved treatment response, and treatment failure occurred in only 29% of patients treated with TIPS implantation [12]. Improved response to treatment and increased survival may be explained by meticulous patient selection, as only patients with recurrent ascites were included in this study. These patients had no more than six paracenteses within the last three months, and patients were allocated to TIPS implantation after a mean of 4.5 paracenteses indicating that these patients did not fulfil the definition of refractory ascites [12]. These facts highlight the rationale for early allocation to TIPS implantation.

The benefit of timely TIPS implantation (i.e. following recurrent ascites instead of refractory ascites) was supported by the study from Piecha et al. [13]. In this study, a higher frequency of paracenteses as a surrogate marker for the duration of decompensation and a high serum creatinine were associated with a reduced clearance of ascites after TIPS implantation [13]. These data support to expand the concept of “early TIPS implantation” to patients with ascites. Balcar et al. analysed the clinical course of patients with ascites as the first decompensating event. They were able to show that patients with grade 2 ascites and a MELD score ≥ 15 as well as patients with grade 3 ascites irrespective of the MELD score had a high risk of further decompensation and increased risk for death [14]. We hypothesise that these patients may benefit from early TIPS implantation. This highly relevant clinical question has not yet been addressed in a prospective randomised controlled trial. Therefore, we aim to analyse the concept of “early TIPS implantation” in these selected patients with liver cirrhosis and ascites as the first single decompensating event.

### Objectives {7}

The primary objective of this study is to assess a survival benefit in patients with early allocation to TIPS implantation in comparison to patients with SMT. The secondary objectives aim to assess the efficacy of TIPS implantation on the course of liver disease and quality of life (QOL).

### Trial design {8}

The eTIPS study is a prospective, randomised, open, multicentre interventional, superiority trial. Patients will be randomised 1:1 in the intervention group with TIPS implantation and in the SMT group. Blinding is not possible because of the interventional character of TIPS implantation.

We hypothesise that early TIPS implantation in cirrhotic patients with first decompensation with ascites leads to improved transplantation-free survival compared to SMT. The trial design is shown in Fig. 1.

**Fig. 1 Fig1:**
[figure not shown]
Trial design of the eTIPS study (created with biorender.com)

## Methods: participants, interventions and outcomes

### Study setting {9}

This is a multicentre trial that will be performed in approximately 10 tertiary academic centres in Germany that are highly experienced in the management of patients with advanced chronic liver disease, portal hypertension and TIPS implantation. List of participating sites can be obtained from continuously updated entries found in the registry on clinicaltrials.gov and in the German registry for Clinical Trials (DRKS). If necessary, additional qualified centres can be included during the study period. All participating centres must provide a multidisciplinary team including hepatologists, interventional radiologists (only in case TIPS implantations are performed by them), intensive care and general surgery with expertise in liver surgery and liver transplantation. The TIPS procedure should be done by an interventional radiologist or an interventional hepatologist who has experience in this procedure (performance of at least 5 TIPS intervention under supervision and at least 15 TIPS procedures without supervision). This qualification will be asked during the site selection visit by self-assessment. If there are personal changes during the study period, the sites are responsible for providing these data for the persons involved in TIPS implantation.

### Eligibility criteria {10}

The eligibility criteria are summarised in Table 1. No gender ratio has been stipulated in this trial as the results of the preclinical and clinical studies did not indicate any gender effect of the trial treatment in terms of efficacy and safety.

**Table 1 Tab1:** Eligibility criteria

Inclusion criteria	Exclusion criteria
Patients eligible for inclusion in this trial must meet *all* of the following criteria:	Patients eligible for this trial must *not* meet any of the following criteria:
1. Patients ≥ 18 years and < 80 years. (Patients > 80 years independent of their physical constitution are excluded as they show higher complication rates and mortality after TIPS implantation) 2. Liver cirrhosis as documented by previous liver biopsy or by a combination of typical clinical, biochemical and sonographic features 3. Ascites as the first single decompensating event with grade 2 ascites and MELD ≥ 15 or grade 3 ascites [1] 4. Ability to understand the nature of the trial and the trial related procedures and to comply with them	1. Treatment refractory or recurrent ascites at the time of study inclusion 2. Patients with concomitant variceal bleeding fulfilling the criteria for pre-emptive TIPS implantation (Child–Pugh class C < 14 points or Child–Pugh class B > 7 with active bleeding at initial endoscopy or hepatic venous pressure gradient [HVPG] > 20 mmHg at the time of bleeding) 3. Budd-Chiari syndrome 4. Portal vein thrombosis (PVT) 5. Spontaneous bacterial peritonitis (SBP) 6. Uncontrolled systemic infection (defined as an increase of > 20% if inflammatory parameters [C-reactive protein, procalcitonin, leukocytes] and/or sepsis as a reason for development of ascites 7. Cardiac cirrhosis (defined as the development of liver cirrhosis in a patient with cardiac heart failure due to primary cardiac disease) 8. Clinical significant cardiac disease (NYHA ≥ II) 9. Untreated valvular heart disease: middle to high-grade valve stenosis or insufficiency (applies to mitral, tricuspid, aortic and pulmonary valves) 10. Diastolic dysfunction grade III, stated by transthoracic echocardiogram (TTE) 11. Reduced left ventricular ejection fraction ≤ 50% 12. Pulmonary hypertension (mean pulmonary arterial pressure > 45 mmHg) 13. Bilirubin > 3 mg/dl 14. Obstructive cholestasis 15. Hepatorenal syndrome type AKI 16. Acute on chronic liver failure 17. Benign liver tumor e.g. cysts within the potential puncture tract 18. Patient after liver transplantation 19. Prior TIPS implantation 20. Ongoing and/or recurrent hepatic encephalopathy (grade ≥ II) 21. Active tumor disease including hepatocellular carcinoma defined as need for chemotherapy, radiation therapy, interventional or surgical treatment 22. New onset of antiviral treatment for chronic hepatitis B virus (HBV) infection within the last 3 months 23. Untreated chronic hepatitis C virus (HCV) infection 24. Life expectancy < 1 year 25. Pregnant or breastfeeding women 26. Patients without legal capacity who are unable to understand the nature, significance and consequences of the study or who are judged as non-compliant (e.g. due to active drug abuse, severe alcohol abuse) 27. Simultaneous participation in other interventional trials which could interfere with this trial; simultaneous participation in registry and diagnostic trials is allowed 28. Person who is in a relationship of dependence/employment with the sponsor or the investigator

#### Who will take informed consent? {26a}

Cirrhotic patients with ascites as the first single decompensating event with grade 2 ascites and MELD score ≥ 15 **or** grade 3 ascites will be screened for eligibility. If a patient appears to be eligible for the trial, the investigator will inform the patient about the trial and ask the patient for his/her written consent. It is imperative that written consent is obtained prior to any trial-specific procedures. Importantly, the screening examinations are performed during routine clinical management and are not exclusively related to the study participation so that they may be performed prior to written informed consent.

#### Additional consent provisions for collection and use of participant data and biological specimens {26b}

Blood and urine samples are collected during the study period at pre-defined timepoints. No additional biological specimens will be sampled.

## Interventions

### Explanation for the choice of comparators {6b}

Currently, TIPS implantation is recommended for patients with liver cirrhosis and refractory or recurrent ascites [1, 7]. However, response to treatment (ascites clearance) is often reduced in these patients with advanced liver disease and long-standing decompensation with ascites [13, 15]. Therefore, we hypothesise that early TIPS implantation in selected patients with ascites as the first decompensating event (grade 2 ascites and MELD ≥ 15 or grade 3 ascites) will lead to a higher rate of ascites clearance and improved transplantation-free survival. Therefore, patients with grade 2 ascites and MELD score ≥ 15 or grade 3 ascites as the first single decompensating event will be randomised in an early TIPS group in addition to standard of care and in a SMT group. Patients in the SMT group will be treated following current evidence-based treatment guidelines [1], and therefore, the SMT group reflects the current approach in treatment of patients with ascites. All patients (also including patients in the TIPS group) are advised to adhere to moderate restriction of sodium intake (80–120 mmol/day = 4.6–6.9 g of salt) according to the current EASL guidelines [1, 16]. Treatment of ascites will be performed according to current evidence-based treatment guidelines. Diuretic treatment (using an anti-mineralocorticoid drug and/or loop diuretics) will be used by clinical judgement under regular control of renal function, sodium and potassium values. The body weight loss should not exceed 0.5 kg/day in patients without peripheral oedema and 1 kg/day in the presence of peripheral oedema. The dose of diuretics can be increased after 72 h of treatment until the maximum dose (spironolactone, 400 mg/day; furosemide, 160 mg/day; torasemid, 40 mg/day) is reached or diuretic-induced complications occur [1, 16]. Diuretic-induced complications are defined as acute kidney injury (defined according the KDIGO criteria) and/or diuretic-induced hyponatraemia (decrease of serum sodium by > 10 mmol/l or to a serum sodium < 125 mmol/l) and/or diuretic-induced hypo-or hyperkalaemia (changes in serum potassium to < 3 mmol/l or > 6 mmol/l despite appropriate measures) and/or disabling muscle cramps.

In patients with grade > 2 ascites, LVP will be performed according to current recommendations. Plasma volume expansion with albumin infusion will be performed following completion of LVP (albumin 8 g/l of ascites drained). If less than 5 l of ascites was drained, no plasma expansion is necessary [1].

The current Baveno VII guidelines make a strong recommendation for the use of non-selective beta-blockers (NSBB; preferred carvedilol or propranolol) for the prevention of decompensating events and therefore, this will be a common co-medication in the SMT group. NSBB should be stopped in case of acute kidney injury (AKI) and persistently systolic blood pressure < 90 mmHg or mean arterial pressure < 65 mmHg. After blood pressure returns to normal and AKI is resolved, NSBB can be restarted [7].

In case of development of overt hepatic encephalopathy, treatment will be started incorporating lactulose (10 ml twice or more daily as necessary) and/or rifaximin 550 mg twice daily [17].

### Intervention description {11a}

TIPS implantation has emerged as an important interventional treatment option in patients with decompensated liver cirrhosis. It leads to a significant decrease in portal vein pressure and effective control of portal hypertension related complications [5].

A high-resolution flat-panel X-ray C-arm with digital subtraction angiography is necessary. During TIPS implantation, vital signs including non-invasive blood pressure monitoring, heart rate, electrocardiogram and peripheral oxygen saturation are monitored.

TIPS implantation will be performed by experienced interventional hepatologists or radiologists (performance of at least 5 TIPS interventions under supervision and at least 15 TIPS procedures without supervision). Before TIPS implantation, LVP may be necessary to facilitate the TIPS procedure. This paracentesis will be documented on the TIPS implantation page in the eCRF and will not be considerd as a secondary endpoint.

A central vascular access for TIPS implantation is obtained by introducing a sheath (10F) in the right internal jugular vein. If the right jugular vein cannot be assessed due to thrombosis or other vascular abnormalities, the left internal jugular vein should be used. Under fluoroscopic and sonographic guidance, the TIPS needle is inserted in the hepatic vein (normally right or middle hepatic vein) and the needle is introduced through the liver parenchyma towards the (right) portal vein branch. It is recommended to use ultrasound guidance for the transhepatic puncture of the portal vein. After the portal vein has been assessed, a guidewire is introduced in the splenic vein or in the superior mesenteric vein. Portography is performed and the portosystemic gradient (PSG) is measured [7, 18, 19]. PSG is calculated as the difference between the inferior vena cava (IVC) and the pressure in the main portal vein. In addition, the pressure in the right atrium is measured. After a PSG > 10 mmHg has confirmed portal hypertension, the parenchymal tract is dilated with a 6-mm dilation balloon. An 8–10 mm controlled-expansion polytetrafluoroethylene (ePTFE)-covered stent is introduced and the stent graft is implanted. It is important that the stent is placed sufficiently within the liver vein (close to the IVC). In patients who are suitable for liver transplantation, the location of the stent is important. A too proximal stent position (stent direct to the right atrium) and too distal stent position (close to the confluence) must be avoided.

Only covered stents with controlled expansion must be used in this trial. The stent will first be dilated to 6 mm and the PSG is measured. If PSG will not show reduction to levels lower than 12 mmHg or no pressure reduction of more than 50% has been reached, the stent will be dilated to a diameter of 8, 9 or 10 mm until the reduction of PSG reaches the target pressure range (PSG < 12 mmHg or PSG reduction > 50%).

 Between each dilation, PSG must be measured and documented. In addition, systemic haemodynamic parameters (blood pressure and heart rate) at the time of PSG measurements must be added to the documentation.

If portosystemic collaterals are detected during portography, these varices or major collaterals can be embolised using metallic coils or glue according to the interventionalist’s choice, especially if these collaterals lead to a steal phenomenon with reduced inflow into the TIPS stent. TIPS implantation will normally be performed in deep sedation using centre specific sedation regimes [20]. According to local standard, general anaesthesia is permitted within the trial. Importantly, sedation has a significant impact on pressure values and therefore, a second measurement of the portal vein pressure and the pressure in the IVC and right atrium should be performed 24–72 h after TIPS implantation. If necessary, however not recommended, mild sedation with low-dose midazolam (0.02 mg/kg body weight) is permitted [7].

TIPS implantation is performed with X-ray fluoroscopy. Approximately 20 min of X-ray fluoroscopy is necessary for TIPS implantation. The second pressure measurement requires a maximum of 5 min X-ray fluoroscopy. It is within the responsibility of the interventionalist to take measures to reduce X-ray exposure (reducing the X-ray field and rate of fluoroscopy). Contrast medium is used for visualisation of vessels, and it should be reduced to a minimum. If locally available, CO_2_ angiography can be used.

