**Secondary**	
The secondary objectives aim to assess the efficacy of TIPS implantation on the course of liver disease and quality of life (QOL)	The following outcome parameters are defined as secondary endpoints: • Time to ascites with need for paracenteses^#^ (Estimand 2) • Quality of life assessed with the SF-36 and CLDQ (chronic liver disease questionnaire) 6 and 12 months after randomisation (Estimand 3)
**Safety**	• Adverse events (AEs), and severe adverse events (SAEs), incidence of complications related to TIPS implantation (incl. technically unsuccessful TIPS implantation) • Rate of TIPS dysfunction • Rate of TIPS implantation in the SMT group

^#^Ascites with need for paracenteses will be classified as following, taking into account the *abdominal distention* caused by ascites [1]: (I): Ascites grade 1(mild): ascites is detectable only by ultrasound examination; (II): Ascites grade 2(moderate): ascites causes moderate symmetrical distension of the abdomen; (III): Ascites grade 3 (severe, large/gross ascites): it causes marked abdominal distension. If patients develop symptoms due to ascites (pain, abdominal tension, dyspnoea), paracentesis should be performed. Date of paracentesis, volume removed and albumin replacement/dose are documented for each paracentesis. Recurrent ascites according to the Baveno VII recommendations is defined as a requirement of 3 or more large-volume (greater than 5 L) paracenteses per year (only paracenteses in stable conditions without infections are considered)[7]

#### Estimand 1

The primary estimand that corresponds to the primary trial objective to show superiority of early implantation of a TIPS in patients with liver cirrhosis and ascites compared to standard medical treatment based on the primary endpoint transplantation-free survival is specified by the following 5 attributes.

*Population:* [A] The population targeted by the primary estimand will be called full analysis set (FAS). This means that the patients will be analysed in the treatment arms to which they were randomised. All randomised patients will be included in the FAS.

*Treatments***:** The randomised experimental arm (TIPS implantation) is compared to the randomised control arm (SMT) of ascites regardless of dosing modifications, treatment interruptions, treatment discontinuation and regardless of intake of additional medications.

Treatment groups are called early TIPS and standard medical treatment.

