### Definition of the secondary estimands

#### Estimand 2

Estimand 2 that corresponds to the secondary trial objective to assess the efficacy of TIPS implantation on the course of liver disease is specified by the following 5 attributes. *Population: [A], Treatments: [A].*

*Variable (endpoint):* The endpoint is ascites with need for paracenteses defined as time from randomisation to date of paracentesis.

*Intercurrent events*: transplantation, death will be considered as competing events.

*Population-level summary:* The population-level summary is defined by the statistical analysis approach which is described below.

#### Estimand 3

Estimand 3 that corresponds to the secondary trial objective quality of life is specified by the following 5 attributes.

*Population [B,C]:* 6, 12-month survival of FAS *Treatments:* [A].

*Variable (endpoint):* The endpoint is quality of life measured by SF-36 and CLDQ.

*Intercurrent events:* There are no intercurrent events not already addressed by the specification of population, treatments and variables.

*Population-level summary:* The population-level summary is defined by the statistical analysis approach which is described below.

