### Participant timeline {13}

Table 3 summarises the participant timeline including the assessments at each visit.

**Table 3 Tab3:** Visit schedule and assessments

	**Screening** **(Baseline day)** **−28–0**	**Visit 1** **Rando** **Day 0**	**Visit 2 ****Intervention** **Day ****1–7** after Rando (only TIPS group)	**Visit 3 ****Discharge ****4 days** after intervention** (+ 7/−2 days) **(only TIPS group))	**Visit 4 ****M1 ****1 month **after Rando **(+ 2 weeks)**	**Visit 5 ****M3 ****3 months **after Rando **(± 4 weeks)**	**Visit 6 ****M6 ****6 months **after Rando **(± 4 weeks)**	**Visit 7 ****M9 ****9 months **after Rando **(± 4 weeks)**	**Visit 8 ****M12** **12 months** after Rando **(± 4 weeks)**	**FU ****Every 6 Month until EOS***^**2**^
Informed Consent	x									
Registration (i.e. entry of first data in eCRF)	x									
Inclusion-/Exclusion criteria	x									
Randomisation		x								
Demographics	x									
Medical history	x									
Physical examination, vital signs	x									
Pregnancy test	x									
12-lead ECG	x									
Colour Doppler ultrasound	x			x	x	x	x	x	x	
Echocardiography (TTE)	x						x			
TIPS (according randomisation)			x							
Laboratory (haematology, clinical chemistry, coagulation)	x**		**:	x	x	x	x	x	x	
Urinalysis	x						x			
Clinical scores^1^	x			x^1^	x^1^	x^1^	x^1^	x^1^	x^1^	
Paracentesis	(x)									
SF-36, CLDQ	x						x		x	
Survival status, liver transplantation				x	x	x	x	x	x	x
Concomitant medication	x	x	x	x	x	x	x	x	x	
(S)AEs	x	x	x	x	x	x	x	x	x	x

*CLDQ *Chronic Liver Disease Questionnaire, *ECG* electrocardiography, *FU* follow up,* Rando* randomisation,* SF-36* Short Form Health Survey (questionnaire)

^*^EOS = end of the entire study is defined as 12 months after randomisation of the last patient

^**^Laboratory tests in screening must be carried out as close as possible to randomisation

(1) Clinical scores include: HE (West Haven Criteria), MELD, MELD Na, MELD 3.0, FIPS, CLIF-C AD, Child-Pugh and NYHA will be documented in eCRF at screening; thereafter, only HE (West Haven Criteria) and NYHA will be collected in eCRF beginning from Visit 3

(2) Only the first paracentesis which is necessary after the study period of 12 months is documented including the date of paracentesis. Further paracenteses after the first one in FU are not considered

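### The tap that prepares for TIPS is exempt from the time-to-paracentesis endpoint, but an SMT patient drained for the same presenting ascites in the same week has an event

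*Protocol article*

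**What the plan says.** Estimand 2 sets the time origin and the event: "The endpoint is ascites with need for paracenteses defined as time from randomisation to date of paracentesis". Its population is that of Estimand 1: "All randomised patients will be included in the FAS". Death and transplantation are competing events, and the arms are compared by a Cox model for the event-specific hazard with a two-sided Wald test (Statistical methods {20a}).

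Table 3 (Participant timeline {13}) places the intervention visit on days 1 to 7 after randomisation, in the TIPS group only. The section Intervention description {11a} states: "Before TIPS implantation, LVP may be necessary to facilitate the TIPS procedure". It then says of that tap: "This paracentesis will be documented on the TIPS implantation page in the eCRF and will not be considerd as a secondary endpoint".

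For ascites treatment in general, the comparator section {6b} states: "In patients with grade > 2 ascites, LVP will be performed according to current recommendations". The footnote to Table 2 adds: "If patients develop symptoms due to ascites (pain, abdominal tension, dyspnoea), paracentesis should be performed". Neither place sets a start-up period. Patients enter with this condition: "Ascites as the first single decompensating event with grade 2 ascites and MELD ≥ 15 or grade 3 ascites".

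The exemption stands only in the intervention section. Estimand 2 does not contain it. Table 4 lists TIPS implantation and revision for this endpoint as not available or event, and does not mention a preparatory tap.

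**The concern.** Every patient has clinically evident ascites at presentation, and some will still need drainage in the first week after randomisation. In the TIPS arm, a drainage done before the procedure to make it easier is not an event. In the SMT arm, a drainage of the same presenting ascites on the same day is an event, and it ends that patient's event-free time almost at once. The scoring therefore depends on the arm and not only on the course of the ascites.

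The trial is open, and the site decides whether a tap was preparatory. A symptomatic tap in a TIPS patient awaiting the procedure could be recorded as preparatory; an SMT patient has no such category. The endpoint carries the protocol's hypothesis of better ascites control, so an artefact here could be reported as a treatment benefit.

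**Working it through.** **Where the rules diverge.** Consider a patient with grade 3 ascites, randomised on day 0 and drained on day 3.
- TIPS arm, tap done to prepare for TIPS on day 4: no event; the patient stays at risk.
- TIPS arm, tap done after the stent is placed: an event, because the exemption does not cover it.
- SMT arm, tap for symptoms or as LVP for grade 3 ascites: an event on day 3.

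Only the first case is exempt, and it can arise only in the TIPS arm. That fixes the direction of the bias.

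**Inputs for the size.** The protocol states no event rate or sample size for this endpoint, so there is no figure of its own to reproduce; its 57 events concern transplantation-free survival.
- From the protocol: 134 patients, 1:1, so 67 per arm. One-year transplantation-free survival is 66% under SMT, used here as the competing hazard in both arms: μ = −ln(0.66) = 0.416 per year. Recruitment takes 36 months and the study ends 12 months after the last randomisation (Table 3), so follow-up runs from 1 to 4 years.
- Assumed: a share p of patients is tapped in days 0–7; the 12-month risk q of a later paracentesis is 40% or 60% in both arms; there is no treatment effect. Every first-week tap is exempt in the TIPS arm. If some of them count there, the bias is smaller.

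**Hand approximation.** Let λ = −ln(1−q) and θ = λ + μ. With follow-up uniform on 1 to 4 years, mean time at risk is

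T = (1/θ) × [1 − (e^(−θ) − e^(−4θ)) / (3θ)].

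The TIPS event rate is λ. In SMT a share p has an event at about time zero, so the rate is λ + p/[(1−p)T]. The apparent rate ratio is

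λ / {λ + p/[(1−p)T]}.

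- q = 40%: λ = 0.511, θ = 0.926, T = 0.935. At p = 20%: 0.25/0.935 = 0.267, and 0.511/0.778 = 0.66.
- q = 60%: λ = 0.916, θ = 1.332, T = 0.702. At p = 20%: 0.25/0.702 = 0.356, and 0.916/1.272 = 0.72.

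**Simulation.** The event-specific Cox model with a Wald test gives nearly the same values (ranges cover q = 40–60% and simulation noise):

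| p | Early SMT events (67 × p) | Hand ratio | Simulated HR | Two-sided 5% tests rejecting |
|---|---|---|---|---|
| 0% | 0 | 1.00 | about 1.0 | about 5% |
| 2% | 1.3 | 0.96–0.97 | about 0.96 | about 5% |
| 5% | 3.4 | 0.90–0.92 | 0.90–0.92 | 6.5–6.8% |
| 10% | 6.7 | 0.81–0.85 | 0.80–0.86 | 12–14% |
| 20% | 13.4 | 0.66–0.72 | 0.66–0.73 | 32–40% |
| 30% | 20.1 | 0.53–0.60 | 0.54–0.62 | 62–74% |

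From p = 10% upward, practically all rejections favour TIPS.

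**Sensitivity to follow-up.** T grows with follow-up, so longer follow-up dilutes the bias and shorter follow-up enlarges it. With 12 months only, p = 5% gives HR 0.86–0.90 and p = 20% gives 0.57–0.68.

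**Check of a common rule.** With days 0–7 ignored in both arms, the null simulation (12 months' follow-up) gives HR 0.995–1.02 and a rejection rate of 4.4–5.4%.

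**The case against.** The exemption has a sound purpose. A tap done to ease access is part of the procedure and would not happen under SMT. Counting it would let the intervention trigger its own failure event and would bias against TIPS. This stands, and it is why simply deleting the exemption is not the remedy. It does not explain why drainage of presenting ascites in the same week should count in SMT.

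A reader might infer that every tap in days 0–7 is exempt in the TIPS arm. The text does not say so: only the LVP that facilitates TIPS is exempt, and any other TIPS-arm paracentesis counts.

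A reader might also infer that the bias must be large because everyone enters with ascites. The documents do not support that. Screening runs from day −28 to 0, Table 3 marks paracentesis as optional at screening, and randomisation is performed as late as possible (section {11c}). Taps before randomisation count in neither arm. Patients with grade 2 ascites fall outside the LVP rule for grade above 2, although they may still be tapped for symptoms. All this lowers p, possibly to a level where nothing visible happens. It does not make the rule the same in both arms.

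The statistical analysis plan is not at hand and may hold a common rule. The protocol, however, already fixes a one-sided one.

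**Conclusion.** The asymmetry is in the text and its direction is certain: whenever SMT patients are tapped in days 0–7 while comparable TIPS patients have an exempt preparatory tap, time to paracentesis is biased towards TIPS. The size is not known, because the protocol gives no rate of early taps. Under the assumptions above it runs from negligible at p = 0–2%, through modest at 5%, to serious at 20% and beyond.

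The concern is confined to Estimand 2. It would be wrong to read it as a threat to the trial's main result: transplantation-free survival, its sample size and its 57-event analysis do not use paracentesis. It should be fixed, but it is not critical to the primary conclusion.

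**What to change.** Write one rule for both arms into Estimand 2 and carry it into Table 4:
- Paracenteses in days 0 to 7 after randomisation (through the end of the Visit 2 window) are not events in either arm. A patient tapped in that week stays at risk for the first later paracentesis.
- All randomised patients stay in the FAS, and deaths and transplantations in days 0 to 7 stay as competing events. Starting the risk set at day 8 would drop these events in the very window of the procedure.
- Early taps are listed by arm.
- State how a preparatory tap is scored if TIPS is placed after day 7.

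Add a sensitivity analysis that counts every paracentesis from randomisation in both arms, labelled as conservative against TIPS because it includes procedural taps.

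The cost is a few sentences. Paracentesis dates are already recorded, patient care does not change, and no interim analysis is planned, so the rule can be set before any comparative analysis. The downside is that a few genuine early events, mainly in SMT, are no longer counted. A first-week drainage may also delay the next one, so if early taps are unevenly spread some imbalance remains; the listing by arm would show it.
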